**Methods:**

In this community-based cross-sectional study, self-identified transgender and non-binary (TGNB) people will be recruited through a two-stage time-location sampling approach. First, community settings in which TGNB people gather will be mapped to develop an accurate sampling frame. Secondly, a multistage sampling design is applied involving a stratification based on setting type (healthcare facilities vs outreach events), a selection of clusters by systematic sampling and a simple random selection of TGNB people within each cluster. Participants will complete an electronic self-reported survey to measure sociological, sexual and drug-using behaviors (risk factors) and oral fluid aliquots will be collected and tested for HIV antibodies. Logistic regression models will be used to evaluate risk factors independently associated with HIV infection. The presented study is registered at ClinicalTrials.gov (NCT04930614).

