## Objectives

This protocol describes the setup of a study aiming to provide a first HIV prevalence estimate for a representative sample of TGNB people residing in a Western European country by combining state-of-the-art epidemiological and sociological methods. By applying a Community-Based Participatory Research (CBPR) and Time-Location Sampling (TLS) approach, this study will allow us for the first time (i) to qualitatively build a sociological map of community settings in which TGNB people congregate for building a sampling frame, (ii) to determine the prevalence of HIV infections in the Flemish and Brussels TGNB population and (iii) to identify associated (sexual) risk factors. The study hypothesis is threefold: (i) social networks and settings where TGNB people may congregate exist, (ii) TGNB people have relatively high rates of HIV infection but differences in HIV prevalence across this heterogeneous population may exist and (iii) the HIV prevalence is mainly determined by sexual risk behavior.

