#### Statistical analysis plan

The proportion of HIV infection and 95% confidence interval will be estimated adjusting for clustering and unequal probability of selection. TGNB people who visited sites more frequently had a higher probability of selection in the study. (Individual) weighting factors will be calculated based on the attendance information provided by the participant to adjust for this unequal selection probability. Moreover, the probability of accepting participation and the sampling fraction (number of participants out of total number of eligible attendees at the cluster) will also be taken into account. One can expect that the real number of attendees at outreach events may deviate from the expected number used for the systematic sampling procedure. The actual number of eligible TGNB persons will always be reported in the data collection form and, if needed, weighting factors will be calculated to correct for the potential deviation in sampling probability.

Socio-demographic and geographic characteristics, sexual and drug-related risk factors of the sample will first be summarized by descriptive statistics. Logistic regression models taking into account clustering and using the sampling weights (being inversely proportional to the selection probability) will be fitted to calculate the odds ratio (OR) and 95% CI for each possible risk factor. Nine variables will be queried to map sexual risk behavior among TGNB people and three variables deal with the use of needles or risky blood contacts in the past. Depending on the number of TGNB people with HIV infection, construction of a multivariable model will be considered to estimate adjusted OR (aOR). After constructing a logistic regression model including all confounding factors (e.g. age or country of birth) that had a P<0.05 in univariate analysis, the significant risk factor(s) will then be separately added as explanatory factors to estimate aOR when deemed appropriate. Statistical analyses will be undertaken using the package ‘survey’ in RStudio to fit the above logistic regression models. Marginal models in the ‘survey’ package focus on the population mean response, averaged over all clusters, taking into account clustering and the sampling weights. Sensitivity analyses might be performed to assess the impact of e.g. potential protocol violations on the robustness of the results.

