*Controlled for confounding*. If possible, multivariable logistic regression analysis will be used to control for all confounding factors at the same time (cfr. supra). Factors that are expected to be related with the risk factors of interest and/or HIV infection are age, gender identity, socio-economic status, medical history, ethnicity and (parent’s) country of birth (whether or not born in an HIV endemic country).

*Complete and adequate follow-up and handling missing data*. Exposure and outcome variables will be collected at the same time and no prospective follow-up of participants is foreseen in this study protocol. Of note, one can assume that the response rate for the follow-up questionnaire would be relatively low but all critical study variables are surveyed at the time of data collection. However, participants can be excluded post-test (i) when they do not belong to the target group (e.g. MSM population, residing outside Flanders or Brussels or < 18 years) based on the self-reported questionnaire or (ii) when data were wrongly entered or linked in the database. It is of note that TGNB people who refused to provide an oral fluid sample after completing the questionnaire will be included to detect any systematic difference in their characteristics and risk behavior with those who completed all steps of the study. Since TGNB people with a reactive oral fluid sample will be invited for further confirmation testing on a blood sample, there is also a risk of missing confirmed outcome data. We assure that we will do all within our capabilities to minimize the loss-to-follow-up via intensive follow-up by email and phone. At this stage, we cannot predict the loss of participants for the confirmation testing and, in first instance, both the reactive oral fluid samples as well as the confirmed HIV status will be assessed as outcome variables. For assessing the impact of the missing data on the study results, multiple imputation will be considered as method for adjusting for missing data [49].

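### A confounder-adjusted odds ratio is planned only for risk behaviours that are already significant, so a behaviour masked by confounding is dropped before adjustment and, for weak to moderate effects, the adjusted odds ratios reported are selected upward

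*Protocol article*

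**What the plan says.** The abstract's methods paragraph states the purpose of the regression: "Logistic regression models will be used to evaluate risk factors independently associated with HIV infection". The Objectives section lists the third aim as "to identify associated (sexual) risk factors".

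The Statistical analysis plan section proceeds in this order:

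1. Weighted, cluster-aware logistic models "will be fitted to calculate the odds ratio (OR) and 95% CI for each possible risk factor".
2. The candidates are counted: "Nine variables will be queried to map sexual risk behavior among TGNB people and three variables deal with the use of needles". The second group also covers past exposure to blood, and the two groups make twelve in all.
3. Whether a multivariable model is built at all depends on how many HIV cases are found.
4. If it is built, a confounder model comes first, "including all confounding factors (e.g. age or country of birth) that had a P<0.05 in univariate analysis".
5. Then "the significant risk factor(s) will then be separately added as explanatory factors to estimate aOR when deemed appropriate".

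The Assessment of potential study bias section, under control for confounding, is worded differently: "If possible, multivariable logistic regression analysis will be used to control for all confounding factors at the same time". It names age, gender identity, socio-economic status, medical history, ethnicity and own or parental country of birth as factors expected to be related to the behaviours, to HIV, or to both.

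**The concern.** The twelve behaviours are exposures chosen in advance, and the question is which of them are associated with HIV after allowing for confounders. Only an adjusted estimate answers that. The plan lets the crude estimate, which the protocol itself expects to be confounded, decide which behaviours are adjusted.

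Two consequences follow.

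- **Masking.** If a behaviour is commoner among younger people and prevalent HIV is commoner among older people, the crude OR is pulled towards 1. The behaviour may fail the screen although its adjusted association is clear.
- **Selection.** An aOR shown only because the crude OR was significant comes from samples in which the estimate happened to be high. Crude and adjusted estimates from one sample are strongly correlated, so the aOR inherits the upward shift.

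The study is meant to identify subgroups for targeted prevention, so both an omitted behaviour and an overstated one matter. The screen also saves nothing inside any model: behaviours are added one at a time, so each model carries the confounders plus one exposure whether or not the others were screened out.

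**Working it through.** **Inputs from the protocol.** N = 1322, design effect 2.36 (range 1.51 to 3.72) and HIV prevalence 3% come from the Sample size section. That section and Table 1 also give a group ratio of three (25% exposed), a two-sided 5% level and 80% power. Expected HIV cases: 0.03 × 1322 = 39.7, about 40.

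**Assumptions, not in the protocol.** True ORs of 2 and 2.5, and the age pattern used below.

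**Reproducing the plan's figure.** For 0.06 against 0.005, the stated formula gives 86 in the smaller group. Then 86 × 4 × 2.36 = 812, as in Table 1. The other three rows come out at 1218, 1152 and 1114 against the stated 1213, 1150 and 1110. The setting is therefore understood as the authors used it.

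**Step 1: how often a moderate effect passes the crude test.** With OR 2, 25% exposed and 3% overall, the risks are 0.0473 and 0.0242. Inverting the same formula, with n = 1322/4 = 330.5 divided by the design effect (DE) and r = 3:

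z = [0.0231 × √(3n) − 1.96 × √(4 × 0.03 × 0.97)] / √(3 × 0.0473 × 0.9527 + 0.0242 × 0.9758)

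- DE 1: (0.727 − 0.669)/0.399 = 0.146, power 56%, fails the screen 44%.
- DE 1.51: fails 58%.
- DE 2.36: (0.473 − 0.669)/0.399 = −0.49, power 31%, fails 69%.

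For OR 2.5 the failure rates are 22%, 37% and 52%. This is the power of the crude test. It shows how readily the gate closes, but it is not the harm done by the gate.

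**Step 2: masking.** Two equal age halves; exposure 35% in the younger and 15% in the older; behaviour OR 2.5; age OR 3; overall prevalence 3%. The baseline odds that give 3% are about 0.0120.

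| Cell | Share | HIV risk |
|---|---|---|
| Younger, unexposed | 0.325 | 0.0119 |
| Younger, exposed | 0.175 | 0.0292 |
| Older, unexposed | 0.425 | 0.0349 |
| Older, exposed | 0.075 | 0.0828 |

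- Exposed overall: (0.175 × 0.0292 + 0.075 × 0.0828)/0.25 = 0.0453.
- Unexposed overall: (0.325 × 0.0119 + 0.425 × 0.0349)/0.75 = 0.0249.
- Crude OR: (0.0453/0.9547)/(0.0249/0.9751) = 1.86, against a true adjusted OR of 2.5.

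In 1500 simulated samples of 1322 without clustering, the crude test was significant in about 45% and the age-adjusted test in about 71%. Other runs of the same set-up gave 46% and up to 76%. In 26% of samples the adjusted test was significant but the screen had already removed the behaviour.

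**Step 3: selection of the aOR.** Again without clustering:

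- True aOR 2, age OR 3, exposure unrelated to age: the median aOR is 2.0 over all samples and 2.4 to 2.5 among those passing the screen.
- Masking case, true aOR 2.5: the median is 2.5 over all samples and 3.2 to 3.3 among those passing.

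**Step 4: the protocol's own effect sizes.** Table 1 corresponds to ORs of about 6 to 36. Power for these at N = 1322 and DE 2.36 is 83% to 92%. For 0.06 against 0.01 (OR 6.3), the median crude OR among significant samples is 6.2 at DE 1 and 6.7 at DE 2.36, so there is little inflation.

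**The case against.** Several points on the other side stand.

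- A reader might infer that non-significance will be treated as absence of association. The protocol does not say so, and it commits to a crude OR with a confidence interval for every candidate. All twelve keep an estimate and an upper limit; what is lost is the adjusted one.
- A reader might take the 44% to 69% failure rate at OR 2 as the cost of the rule. It is the crude power of this sample size at an OR the protocol does not plan for, and reporting every aOR would not change it. The 69% end also uses a design effect that the Sample size section calls conservative for individual-level risk factors.
- A reader might infer that all reported aORs will be exaggerated. At the Table 1 effects the inflation is small.
- The masking example is hypothetical. The protocol gives neither direction nor size for the confounding, which could run the other way, and the example presumes that age enters the model. With a weaker pattern (age OR 2, exposure 30% against 20%) the gap shrinks to about 70% against a little under 80%. At DE 2.36 the main example becomes 23% against 40%.
- The text is provisional: the model is only considered, and aORs follow when judged appropriate. The word significant is not explicitly tied to the crude P value.

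The last point does not remove the problem. The crude analysis is the only earlier analysis of the risk factors in that section, so the sentence order leaves no other natural reading. It is a stated rule, not a detail left to a fuller plan.

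**Conclusion.** The point holds in a limited form. The plan restricts adjusted ORs to behaviours that are significant, on the natural reading in the crude analysis. That fits poorly with an aim of independent association and with the protocol's own expectation of confounding.

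Under the stated assumptions, a masked behaviour with a true aOR of 2.5 passes the gate about 45% of the time, against about 71% detection after adjustment. A true aOR of 2 appears as a median of about 2.4 to 2.5 among factors that pass. These figures assume 1322 participants, 3% prevalence, no clustering and the chosen age pattern; they illustrate the mechanism and are not forecasts. For effects as large as those in Table 1 the consequence is minor. The documents do not support saying that behaviours will be declared unrelated to HIV.

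**What to change.** Replace the sentence on adding significant risk factors with wording such as:

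> For each of the twelve pre-specified risk behaviours, the crude OR and the OR adjusted for the same small pre-specified confounder set (chosen from the factors named under control for confounding) will be reported with 95% CI, whatever the crude P value. If the number of HIV cases does not allow a multivariable model, this applies to all twelve alike.

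This also settles the mismatch between screening confounders at P<0.05 in the analysis section and adjusting for all of them together in the bias section.

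The cost is one sentence and at most twelve model fits, with no new data. With about 40 expected cases, one behaviour plus a small confounder set remains feasible, though some adjusted intervals will be wide. The change does not raise the power of the crude test. It removes the selective adjustment and the inflation that comes with it.

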#### Assessment of potential study bias

*Appropriate eligibility criteria*. In contrast to using a convenience sample, TLS allows the recruitment of a more representative study population by approximating random cluster sampling. Against this background, we will ensure that the sample frame will be completed by interviewing a wide range of key informants in terms of gender identity, ethnicity, age and sexual orientation and until saturation occurs. To ensure diversity in healthcare settings, not only large multidisciplinary gender teams will be included, but also independent professionals working in transgender healthcare who are listed on the Transgender Healthcare Map. If necessary, the sampling frame will be updated during the course of the project to avoid the pitfall of missing some settings. Nevertheless, there will be selection bias towards those who need gender affirming medical care and attend the identified events and locations while TGNB people who never or rarely attend have almost zero probability of being sampled. To (partly) address this limitation, online digital spaces will also be identified and included in the sampling frame. Moreover, we propose that the TLS data will be analysed as a two-stage sample survey using a simple weighting procedure based on the inverse of the approximate probability that a person was sampled. Non-response analysis will also be performed to detect differences regarding gender and age between those who participated and those who declined, and unequal probability of accepting participation will be taken into account when calculating weighting factors.

Selection bias can also be introduced if community researchers do not adhere carefully to design and implementation procedures. There will only be a representative sample if there is no deviation from sampling strategies and interviewing respondents for each place and time. This is why all peer data collectors who are involved in field testing will be trained by the main research team to recruit respondents in the same way. A standard operating procedure on recruitment of participants and data collection will be developed paying special attention to potential bias and inclusive and cultural sensitivity.

To roughly verify whether a representative sample was acquired based on the used sampling strategy, the demographic characteristics (age and gender) of the study population will be compared with the current figures on demographic composition of the TGNB population in Flanders and Belgium. However, this comparison should be interpreted with caution since the group of TGNB people who are visible in the current statistics, are probably only the tip of the iceberg

*Appropriate methods for exposure and outcome variables*. Data on exposure of interest will retrospectively be collected through self-administered questionnaires. The quality of the data is therefore determined to a large extent by the person’s ability to accurately recall past exposures to risk factors. Recall bias may result in either an underestimate or overestimate of the association between exposure and outcome. HIV positive participants are often more likely to recall exposure to risk factors than the healthy controls. Moreover, self-reporting data can also be affected by social desirability or approval since the questionnaire includes private and sensitive topics. As a consequence, the results on sexual or drug-using risk behavior could be underreported. Therefore, it is crucial to guarantee confidentiality at the time of data collection [48]. Although participants who are aware of the exact research question are much more likely to cloud their opinions and memories about the risk factors, we will not be able to blind the participants to the study hypothesis for ethical reasons and for guaranteeing a full transparent process to the community. It will also not be possible to blind the peer data collectors to the study hypothesis but they will be trained in data collection and need to adhere to a standardized operating procedure. Furthermore, the peer data collectors will be blinded to the outcome variable (HIV infection). Outcome variables will be collected from saliva analyses with objective and clear diagnostic criteria and the outcome assessors will be blinded to the results of the questionnaire.

*Controlled for confounding*. If possible, multivariable logistic regression analysis will be used to control for all confounding factors at the same time (cfr. supra). Factors that are expected to be related with the risk factors of interest and/or HIV infection are age, gender identity, socio-economic status, medical history, ethnicity and (parent’s) country of birth (whether or not born in an HIV endemic country).

*Complete and adequate follow-up and handling missing data*. Exposure and outcome variables will be collected at the same time and no prospective follow-up of participants is foreseen in this study protocol. Of note, one can assume that the response rate for the follow-up questionnaire would be relatively low but all critical study variables are surveyed at the time of data collection. However, participants can be excluded post-test (i) when they do not belong to the target group (e.g. MSM population, residing outside Flanders or Brussels or < 18 years) based on the self-reported questionnaire or (ii) when data were wrongly entered or linked in the database. It is of note that TGNB people who refused to provide an oral fluid sample after completing the questionnaire will be included to detect any systematic difference in their characteristics and risk behavior with those who completed all steps of the study. Since TGNB people with a reactive oral fluid sample will be invited for further confirmation testing on a blood sample, there is also a risk of missing confirmed outcome data. We assure that we will do all within our capabilities to minimize the loss-to-follow-up via intensive follow-up by email and phone. At this stage, we cannot predict the loss of participants for the confirmation testing and, in first instance, both the reactive oral fluid samples as well as the confirmed HIV status will be assessed as outcome variables. For assessing the impact of the missing data on the study results, multiple imputation will be considered as method for adjusting for missing data [49].

#### Dissemination

This study was registered at Clinicaltrials.gov (NCT04930614). The results of this study will first of all be submitted to a peer-reviewed journals within 12 months of the final data collection date. However, researchers should ensure their research is framed in a way that positively impacts transgender health and minimizes possible harmful utilisation of the results [25]. The results of this study should ultimately benefit transgender health without increasing stigma and discrimination and with respect for the TGNB community. It is advised that, instead of only focussing on academic dissemination of findings, research should be disseminated back to the community and should be accessible to the TGNB community and non-academic healthcare professionals [15, 25]. Therefore, after publication of the results in peer-reviewed journals, the results will be disseminated to a broad public as well as the TGNB community itself by using the general communication channels of the Institute for the Equality of Women and Men (IGVM) and the Transgender Information Point—the Flemish government-funded expertise centre on transgender issues—as well as the social media channels that were set up for the study. The findings of the study will be available in the form of a report as well as a range of infographics and web pages. The researchers will also actively engage with mainstream and transgender specific media channels to establish the intended interpretation of the study results.

## Discussion

Although HIV prevalence has been estimated relatively high in transgender people (roughly 12–28%), current literature has mainly focused on high risk groups, such as female transgender sex workers, and thereby largely neglected intra-group variation within the TGNB community. Up until now, large well-designed studies investigating HIV prevalence and associated risk factors in this heterogeneous population based on HIV diagnostic orientation testing are completely lacking. The protocol of this study was conceptualized to provide the first estimate of HIV prevalence in a representative sample of TGNB people in Flanders and Brussels by combining CBPR and two-stage TLS strategies. The application of this unique combination will allow us to generate a large and broad sampling frame and to systematically collect data from TGNB people attending the clusters in the sampling frame. By associating HIV testing results with the data extracted from behavioral questionnaires, this cross-sectional study not only aims to estimate the HIV prevalence rate in TGNB people residing in a Western European country but also to identify high risk groups within this TGNB community. Such data is needed to develop effective targeted sexual health interventions for TGNB people as well as avoid to stigmatizing and discriminating policies.

The approach of the study presents a number of challenges. First, to obtain an accurate representation of the TGNB population in Flanders and Brussels it is crucial to develop an exhaustive sampling frame of (online) community and healthcare settings covering all aspects of social life in order to minimize the probability of systematically missing target groups. Moreover, another potential limitation of this study is that the assessment of risk factors rely on participants recall to exposed risks in the past 12 months. Lastly, implementing the CBPR approach in this study will be challenging in terms of assuring skills of lay researchers and guaranteeing motivation to adhering to the protocol and data quality [50, 51]. However, the CBPR approach will help us to reach hidden TGNB subgroups and contribute to the acceptability of the study and its methods by the community. To provide a solution for the potential pitfalls, standard operating procedures on participant recruitment, data collection and data quality will be developed to train and coach the lay researchers.

The strength of this study is that it will directly expand our knowledge base and understanding of HIV prevalence rates among the hard-to-reach and vulnerable TGNB population. By systematically identifying all relevant clusters where TGNB people can be reached, and by randomly sampling TGNB people at the sampling clusters, we will be able to generate a representative sample of TGNB people and, hence, to generalize the study findings to the well-defined TGNB population in Flanders and Brussels or even Western Europe. For hard-to-reach populations such as TGNB people, TLS is the most effective method for obtaining probability samples of populations who can be located at well-defined venues.

